## **Recruitment**

### *Outpatient clinics*

Eligible patients will be recruited prior to their physical or telehealth outpatient appointment by trained research staff. Staff will screen clinic lists for all outpatient cardiology clinics and identify patients that meet study inclusion criteria.

These patients will be contacted via telephone by study staff and, if agreeable, will be emailed a link. This link will take participants directly to a study description document, followed by baseline surveys and, depending on intervention allocation, either a message thanking them for their participation or the intervention videos.

If patients are physically attending the hospital for their appointment, they will be offered the study intervention on a study iPad in the clinic waiting room or have the option to participate in the study via their own device prior to the appointment.

### *Inpatients*

Inpatients will be only be approached by study staff after:

- A) The patients treating doctor refers them for recruitment onto the study
- B) Westmead hospital's COVID-19 policies allow research staff to approach hospital inpatients for participation in clinical trials

Hospital inpatients, if recruited, will have the option of receiving the intervention on their own device or to have the intervention delivered on a study tablets (iPad) which will be sanitised between patients.

The consent process is detailed in section 9.3.

## **3.4 Randomisation and blinding:**

### **Overall study**

Randomisation will occur centrally via a computer-generated sequence, using the randomise R library of R statistical software (version 3.5.1), before the study commences. Randomisation will be 1:1 and in randomised permuted blocks of 4 and 2 to reduce predictability and ensure a balance between the two arms.

After registration, patients will be allocated a study number. From there-on, their details will be deidentified. Clinic staff and follow-up outcome assessors will be blinded to the condition patients have been allocated to. However, due to the nature of the intervention, participants cannot be blinded to their treatment allocation.

## **4. Trial intervention:**

### **Control:**

Patients randomised to the control arm will view the study description document, complete baseline surveys and then proceed through usual care. In the clinic waiting room this will involve healthcare posters/pamphlets and a small central TV fixed to a low volume. For inpatients, usual care will vary however may include education provided by medical staff on ward rounds, time spent watching TV and ad-hoc education from other hospital staff.

### **Intervention:**

Patients randomised to the intervention arm will view the study description document and complete baseline surveys. Following this, they will be automatically delivered the series of 4 clinician-developed videos.

Intervention participants will then either receive a link to the intervention videos once/week via text/email.

Reviewers can view the video series at the following link:

<https://vimeo.com/showcase/7683573>

#### 4.1 Intervention development:

The study intervention was developed by investigators AT and JK. The educational audiovisual module was designed to be a web-based combination of four short videos (privately hosted on YouTube) to be viewed sequentially, accompanied by questions gauging patient experience. The module was consolidated using Research Electronic Data Capture (REDCap). Data from the module were collected and coded on REDCap via a secure database.

Investigators decided on an up-to-date, reliable, yet simple syllabus covering the fundamental concepts of the pathophysiology, clinical presentation, diagnosis and management of AF. The four succinct videos within the module encompassed the following topics: (1) 'What is AF?', (2) 'AF Management', (3) 'Stroke risk and anticoagulation', and (4) 'Lifestyle modification'.

The level of patient satisfaction for each individual video, and satisfaction with the videos overall, were recorded on 5-point Likert scales. Further, 0-100 visual analogue scales were used to gauge the patient's response to clinician narration, and the module's utility in improving patient decision making, anxiety around consultation, and long-term treatment adherence. The visual analogue scales and Likert scales were created and combined with the four videos for the audiovisual module using REDCap.

To make the four educational videos within the module, four brief slideshows were created using Microsoft PowerPoint on the laptop, then recorded audio narration simultaneously to annotate the slideshows using the Apple iPad. The videos were subsequently privately hosted on YouTube in order to be consolidated alongside the questions gauging patient experience on REDCap. REDCap then generated a Uniform Resource Locator (URL), also known as a web address, and a Quick Response (QR) code, both of which enabled access to the educational module using any device with Internet access.

All information provided within the module was only included following brief inspection of the latest peer-reviewed literature on the associated topics by the clinician in order to update existing knowledge. The audiovisual module, along with all included images and visual media, was consolidated solely for private use limited to the duration of the study. It was not marketed or sold for commercial purposes.

Following informed consent, patients completed the audiovisual educational module during the otherwise non-utilized waiting time prior to their consultation for AF. Patients accessed the web-based module through either the URL or QR Code generated by REDCap. This was done using either the single Apple iPad that was already owned by the specialist clinic, or mobile smart devices that the patients already owned.

The intervention was then further enhanced by DM and AT utilizing VideoScribe® technology to increase the acceptability of video content.

#### 5. Data Collection and Management:

Baseline, post-clinic and follow up data will either be collected by study staff via phone call and entered remotely into the intervention delivery platform, or entered directly by participants into the delivery platform, RedCap. The study platform will be designed such that it is user friendly across smart phone, tablet and computer. Study staff will be available via phone call to assist patients with data entry and accessing the intervention.

| Survey                                                                | Baseline | Post-clinic/within 2 days of intervention delivery | 90-day follow up |
|-----------------------------------------------------------------------|----------|----------------------------------------------------|------------------|
| Baseline demographic information                                      | X        |                                                    |                  |
| Satisfaction with care (7 – point Likert scale)                       |          | X                                                  |                  |
| Medication adherence                                                  | X        |                                                    | X                |
| Motivation to maintain adherence to AF therapy (7-point Likert scale) | X        | X                                                  | X                |

|                                                 |   |   |   |
|-------------------------------------------------|---|---|---|
| AF Knowledge (Jessa AF Knowledge Questionnaire) | X | X | X |
|-------------------------------------------------|---|---|---|

*eTable 1: Outline of data collection process*

Data will be managed in the RedCap® system during the trial with programmed range checks and sense checks. Physical source data for the end of clinic survey will be stored in a locked office accessible only by card. Primary outcome data will be monitored against source data. At study completion data will be exported for analysis. Exported data files will be stored in secure password-protected servers at the University of Sydney in compliance with ethical commitments. Investigators responsible for data analysis will not be involved in collecting identifiable participant information.

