#### **Hypothesis:**

Patients exposed clinician-developed educational videos prior to and post clinic appointment will higher knowledge of AF, medication adherence and satisfaction with clinical care compared to usual care.

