#### **Specific Aims:**

**To examine, among patients with atrial fibrillation accessing clinical care whether a series of clinician-designed educational videos delivered prior to clinic improves:**

1. Knowledge of AF
2. Adherence to AF-related medication
3. Satisfaction with clinical care

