## **6. Assessment of outcomes:**

### **Primary Outcome:**

The primary outcome will be the difference in participant percentage score on the JESSA Atrial Fibrillation Knowledge Questionnaire (JAFKQ) in the intervention arm with reinforcement compared to the control at 90 day follow up.

Secondary outcomes assessed at end of clinic (outpatients)/within 2 days (inpatients) will include atrial fibrillation knowledge (JAFKQ), satisfaction with clinical care (7-point Likert scale) and motivation to maintain adherence to anticoagulation therapy (7-point Likert scale). Medication adherence will be measured at 90 day follow up (see table 1).

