#### **10.4 Confidentiality**

All personal information in the central database will be de-identified. Participant information sheets and survey responses will be stored in a locked office in the Westmead Applied Research Centre only accessible by card. Data entered via study tablets will be stored in the secure RedCap server. The information will be re-identifiable for the research assistant that will be making 90 day follow up calls to participants.

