### 1.1 Primary objective

To examine, in a randomised controlled trial of 200 hospital inpatients and outpatients with AF, the impact of continued exposure to clinician-created educational videos on AF knowledge at 90 day follow up.

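### The 90-day JAFKQ may be self-entered unsupervised on the platform that delivers the videos, and only the intervention arm is sent the video link, so look-up during the test could favour that arm.

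*Combined protocol and SAP*

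**What the plan says.** **How the primary outcome is collected.** Protocol section 5 gives two routes for baseline, post-clinic and follow-up data: a phone call by study staff, or data "entered directly by participants into the delivery platform, RedCap". That wording makes REDCap both the survey tool and the delivery platform. Protocol 10.3 lists consent to phone contact at 90 days, and 10.4 mentions "the research assistant that will be making 90 day follow up calls to participants". Neither makes the call the required mode for the JAFKQ.

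**Who has the videos.** Protocol section 4 says: "Intervention participants will then either receive a link to the intervention videos once/week via text/email". The sentence is incomplete (an either without an or), and it gives no number of sends and no end. Protocol 10.5 sends the links to all participants only after the 90-day follow-up period. SAP 3.5.1 counts a 90-day survey as inside its window up to 120 days.

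**Blinding.** Protocol 3.4 blinds clinic staff and follow-up outcome assessors, and says that participants cannot be blinded.

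**What strategy is tested.** The descriptions differ:
- Specific Aims: "whether a series of clinician-designed educational videos delivered prior to clinic improves" the listed outcomes.
- Hypothesis: "educational videos prior to and post clinic appointment".
- Protocol section 6, primary outcome: "in the intervention arm with reinforcement compared to the control at 90 day follow up".
- SAP 1.1: "the impact of continued exposure to clinician-created educational videos on AF knowledge at 90 day follow up".
- SAP 1.4: access to four videos, with no repeat sending mentioned.

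**The concern.** The primary endpoint is a knowledge test, and three features of the plan combine to expose it. One arm is repeatedly sent a source that covers the tested material: the video topics in Protocol 4.1 include what AF is, its management, and stroke risk and anticoagulation, while the JAFKQ asks about AF in general and about anticoagulation. Participants in that arm know their allocation. Some of them may sit the test alone, online, through the system that serves the videos. A self-entered survey has no assessor, so assessor blinding gives it no protection.

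If intervention participants look answers up more often than controls do, the 90-day difference contains a component that is not knowledge under any of the plan's definitions, and it points towards the intervention. Because mode of completion is not recorded, the trial could not later show that its primary result was free of this.

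Separately, the delivery descriptions do not agree, so a reader cannot tell which strategy a positive 90-day result would support.

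**Working it through.** **1. The plan's own figure.** Inputs from Protocol section 7 and SAP 1.6: 100 per arm, 15% attrition, SD 18, two-sided 5%, difference 8.95 points.
- Analysed per arm: 100 × 0.85 = 85.
- Standard error of the difference: 18 × √(2/85) = 2.761.
- Detectable difference at 90% power: (1.960 + 1.282) × 2.761 = 8.95.
- Power at 8.95 points: 90.0% by the normal approximation, 89.7% by the noncentral t.

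The stated power reproduces, so the sample size is not in question. The smallest observed difference that reaches significance is 1.960 × 2.761 = 5.41 points.

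**2. What one item is worth.** Protocol section 5 gives everyone 8 general items, those on anticoagulation 5 more, and those on warfarin or a NOAC 3 more. The range is therefore 8 to 16 items. If items are weighted equally (assumed), one item is worth 100/16 = 6.25 to 100/8 = 12.5 points, against a target of 8.95.

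**3. False-positive rate for a given net bias.** Let b be the mean look-up gain in the intervention arm minus that in the control arm. Assume no true effect and SD held at 18. The chance of p < 0.05 is Φ(b/2.761 − 1.960) + Φ(−b/2.761 − 1.960).

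| Net gain b (points) | b/2.761 | Chance of p < 0.05 |
|---|---|---|
| 0 | 0 | 5% |
| 1 | 0.362 | 6.5% |
| 1.75 | 0.634 | 9.7% |
| 2.6 | 0.942 | 15.6% |

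**4. Behaviour that would produce such gains.** Every input in this step is assumed; none is in the documents. Take b as the self-entry share times the difference in look-up share times the points gained, with a gain of 12.5 points (two items of 16).
- 70% self-enter, 20% of those in the intervention arm look up, no controls do: 0.7 × 0.20 × 12.5 = 1.75 points.
- The same with 30% looking up: 0.7 × 0.30 × 12.5 = 2.63 points.
- Controls look up at half the intervention rate: the two gains halve to 0.88 and 1.31 points, and the formula in step 3 gives about 6% and 8%.
- Both arms look up equally, or everyone is tested by phone without aids: b = 0 and the rate is 5%.

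**5. What counts as bias.** SAP 1.1 makes continued exposure the tested strategy, the Hypothesis includes exposure after clinic, and SAP 3.3 and 5.1.2 grade engagement by repeat viewing. A participant who watched the videos the day before the survey and remembers them is showing the effect that the SAP sets out to measure. One who reads the answer off an open video is not.

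**The case against.** **Repeat viewing is intended.** This stands. A reader might infer from the Specific Aims that any viewing after clinic contaminates the 90-day score, so that answers from a recently watched video are not knowledge gained. The Hypothesis, Protocol sections 4 and 6, and SAP 1.1, 3.3 and 5.1.2 do not support that. The Specific Aims wording differs from these passages, which is a matter for reconciliation and not evidence of bias.

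**Phone follow-up is foreseen.** This stands in part. Section 5 names the staff call first, and 10.3 and 10.4 plan for 90-day contact. If most surveys are taken by phone, the exposure is small. But section 5 leaves the choice open and no text gives the call priority for the JAFKQ.

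**Controls can look things up too.** This stands. A control who self-enters is online, and usual care in the clinic includes posters and pamphlets. Only the difference between arms matters. Equal look-up still cannot be presumed when the trial sends a direct link to one arm only.

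**The links may have an end that is not visible here.** Both participant-flow figures are missing from the text available, and SAP 5.1.2 refers to an intervention period. The claim is therefore limited to what the readable text states.

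**The reinforcement wording suggests a third arm.** A reader might infer this from Protocol section 6. The design sections of both documents specify two arms, and all randomised participants are analysed by intention to treat, so the phrase changes no analysis.

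**Conclusion.** The point holds as a weakness in how the primary outcome is collected. Unsupervised self-entry is permitted on the platform that delivers the videos, one arm alone is sent the link, and the readable text has no closed-book instruction, record of mode or stated stop to the links. Look-up during the test could therefore favour the intervention.

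The documents do not show that it will happen or how large it would be. A reader might infer that the 90-day score overstates knowledge or that the type I error is inflated; both depend on behaviour that nobody has observed. The range of 5% to about 16% for net gains of 0 to 2.6 points is an illustration. It rests on SD 18, 85 analysed per arm, no true effect and assumed look-up behaviour. Sample size and power are unaffected.

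The differing delivery descriptions are a separate matter of interpretation. The 90-day result cannot be read as the effect of pre-clinic delivery alone. The change is worth making because it is cheap and the primary endpoint is better protected with it.

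**What to change.** **1. Collection of the JAFKQ.** In both arms, make the 90-day phone call that is already foreseen, carried out by the blinded assessor, the default mode. Keep self-entry as a fallback when the call fails, to limit missing data. Record the mode for every survey and report it by arm. Instruct all participants to answer without the videos or other aids. Add a sensitivity analysis of the primary outcome by mode, read with care because mode is settled after randomisation. Apply the no-aids instruction and the record of mode to the post-clinic JAFKQ as well: it can be self-entered in the same way, so it is no cleaner a test of pre-clinic delivery.

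**2. Wording.** The sponsor should reconcile the delivery descriptions in the Specific Aims and SAP 1.4 with those in the Hypothesis, Protocol sections 4 and 6, and SAP 1.1. It should also state when the weekly links stop relative to the 90-day survey, bearing in mind the 120-day window. In line with SAP 1.1 as it stands, word the 90-day conclusion as the effect of continued access to the videos in all participants randomised to intervention, not of pre-clinic delivery alone.

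**Cost.** Text edits, one recorded field and a slightly longer call, with staff already in the plan. There is some risk that participants reveal their allocation to the assessor, and some surveys that would have been self-entered may be lost. A call makes look-up harder but does not rule it out.

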**Baseline demographic information:**

Baseline demographic collection will include:

- Gender
- Age
- Ethnicity
- Educational level
- AF subtype
  - o Atrial fibrillation or atrial flutter
  - o Non-valvular or valvular
  - o First AF episode or paroxysmal ongoing AF or persistent AF or permanent AF or predominant atrial flutter
  - o Time since AF diagnosis
- Medical history (diabetes, hypertension, coronary artery disease, stroke, peripheral vascular disease, hyperlipidemia, chronic kidney disease)
- Current medications

AF subtype, medical history and current medications will be collected separately from hospital records by study staff. All other information will be collected in the baseline study assessment form.

**Jessa Atrial Fibrillation Knowledge Questionnaire:**

The Jessa Atrial Fibrillation Knowledge Questionnaire (JAFKQ) has been developed by Deteghe et al (2016).(6)

The questionnaire will be delivered to participants such that:

- All participants answer the first 8 questions (1.1 – 1.8) on general AF knowledge
- ONLY participants on anticoagulation answer questions on anticoagulation (2.1 – 2.5)
- ONLY patients on Warfarin answer questions 3.1-3.3
- ONLY patient on novel oral anticoagulation (NOAC) answer questions 3.4-3.6

**Medication adherence:**

To assess medication adherence, we will utilise 3 questions adapted for from the Coronary Artery Risk Development in Young Adults (CARDIA) study. This series of questions has previously been used to assess adherence to hypertensive medications in patients with coronary artery disease, and since in a large scale cross sectional study of patients with atrial fibrillation. The questions are:

- 1) **Specific to your atrial fibrillation medication, in the past month, how often did you take your medications as the doctor prescribed?**
  - a. All of the time (100%)
  - b. Nearly all of the time (90%)
  - c. Most of the time (75%)
  - d. About half the time (50%)
  - e. Less than half the time (<50%)
  - f. No atrial fibrillation medication
- 2) **Specific to your atrial fibrillation medication, in the past month, how often did you forget to take one or more of your prescribed medications?**
  - a. Never

- b. Once
- c. 2-3 times
- d. Once per week
- e. Several times per week
- f. Nearly every day
- g. No atrial fibrillation medication

3) **Specific to your atrial fibrillation medication, in the past month, how often did you decide to skip one or more of your prescribed medications**

- a. Never
- b. Once
- c. 2-3 times
- d. Once per week
- e. Several times per week
- f. Nearly every day
- g. No atrial fibrillation medication

Non-adherence will be defined as per previous studies:

1. Response to question 1 of “Most of the time (75%) or less
2. Response to question 2 of “once per week” or more
3. Response to question 3 of “once per week” or more

## **6. Assessment of outcomes:**

### **Primary Outcome:**

The primary outcome will be the difference in participant percentage score on the JESSA Atrial Fibrillation Knowledge Questionnaire (JAFKQ) in the intervention arm with reinforcement compared to the control at 90 day follow up.

Secondary outcomes assessed at end of clinic (outpatients)/within 2 days (inpatients) will include atrial fibrillation knowledge (JAFKQ), satisfaction with clinical care (7-point Likert scale) and motivation to maintain adherence to anticoagulation therapy (7-point Likert scale). Medication adherence will be measured at 90 day follow up (see table 1).

### **7. Statistical considerations and Analysis:**

Analysis will follow intention to treat principles with all participants analysed in the arm they have been randomised to. P-values of  $< 0.05$  will be considered significant. Primary outcome analysis will use a two-tailed t-test to assess the difference between mean participant JAFKQ scores (max score = 100). Analysis will also be performed utilizing an Analysis of Covariance (ANCOVA), with baseline JAFKQ scores and education level incorporated into the model as covariates. A sample size of 200 participants (100 per arm) would, allowing for 15% attrition and assuming a standard deviation of 18 as described in other studies, have 90% power (2 sided, type 1 error of 5%) to detect an difference in 90-day AF knowledge of 8.95% between participants in the intervention and control arms of the study, which we consider a significant improvement in knowledge. Previous assessment of the JAFKQ has indicated participant scores 1 month post-test with no educational intervention are unchanged (60.4 [SD = 18.6] vs 62.3 [SD = 18.5];  $p = 0.551$ ).

For secondary analysis of satisfaction with clinical care, patient responses will be dichotomised into ‘satisfied’ ( $\geq 5/7$ ) vs ‘unsatisfied’ ( $\leq 3/7$ ). For medication adherence, patients will be classified as “adherent” or “not adherent as per page 11-12. Proportions in intervention vs control arms will be compared using a chi-squared test. Relative risk will be calculated using a log binomial unadjusted and adjusted for total time in clinic (for outpatients) and number of medications. Allowing for 15% attrition and assuming 60% satisfaction/medium or greater adherence in the control groups, a sample size of 200 (100 per arm) would have 90% power to detect a relative risk difference in satisfaction and adherence between control and intervention groups of 1.37 (that is, an increase from 60.0% to 82.2%).

